##### Clinical assessment at baseline and 6 months only

grip strength (JAMAR) [33], pinch strength (B & L pinch gauge) [33], functional performance using the grip ability test (GAT) [32]. (See Tables 4 and 5).

#### Diary

All participants randomised to the trial will be given a diary to complete at baseline (nurse clinical assessment) and at 6 months (the primary end point). The diary is based upon the Activity Record (ACTRE) for patients with musculoskeletal disorders [53,54]. The diary aims to capture hand pain and functional limitation experienced when carrying out main activities for each half hour during a typical weekday and a weekend day, along with any rest periods taken during the activities. For each main activity, in each half hour period, participants will rate their hand pain and hand disability on a 0-3 scale, where 0 represents 'no hand pain/disability' and 3 represents 'a lot of hand pain/disability'. The 6-month diary will also include open ended questions to ask participants if they feel they have benefitted from taking part in the study and if not what they feel would have been beneficial. Participants will also be invited to make any additional comments if they wish.

#### Target sample size

The main study sample size calculation will be based on the comparison of participants receiving and those not receiving hand exercises. The calculation would be identical for the comparison of joint protection versus no joint protection, as hand exercises and joint protection are assumed equally effective and independent treatments [55].

In participants not receiving hand exercises 50% will receive a leaflet and advice, and 50% will receive joint protection. We estimate that 25% of participants in the leaflet and advice group will improve using the OARSI-OMERACT responder criteria and 45% will improve in the joint protection group [42,56]. This gives a combined improvement of 35% in participants not receiving hand exercises, assuming equal allocation of participants between treatment groups.

Published information is not available to define a minimum clinical important difference for the primary outcome measure. Therefore, after a consensus discussion with the OTs we estimate this at 20%, and hence the estimate of improvement in the group who receive hand exercises to be 55% (i.e. 35% + 20%). To detect a difference of 20% or larger between participants receiving and those not receiving hand exercises, with 80% power and alpha of 5%, a total of 212 participants with data at baseline and at 6 months are required. To allow for a 15% drop-out over the 6 months post randomisation period, 252 participants will be randomized, i.e. 63 per treatment arm.

#### Statistical methods, between group comparisons, handling of non-adherence and missing data

The main statistical analysis will be based on reporting guidelines for the design and conduct of factorial trials [55] and will be conducted for all primary and secondary outcomes. The main treatment analysis will be conducted blinded to treatment allocation and will be analysed on an intention to treat basis with all randomised participants retaining their original randomised group. Outcome measures that are continuous will be analysed using analysis of covariance (ANCOVA); for binary outcomes, logistic regression will be used. The data will be analysed at 3, 6 and 12 month follow-up, however, 6 months is the primary end point for the study.

An initial treatment model will be fitted (for each primary and secondary outcome and end-point) to predict the outcome of interest and will include the two treatment effects of interest: no joint protection versus joint protection; no hand exercises versus hand exercises, and their interaction. If the interaction term is not statistically significant (p > = 0.05) it will be dropped from the model. The model will be re-run, and the treatment effects for joint protection and hand exercises determined individually from this model, either as mean differences or odds ratios with associated 95% confidence intervals, as appropriate. If the interaction term is statistically significant (p < 0.05), the effect of joint protection and hand exercises will be evaluated from a model with treatment represented as a 4-level variable (i.e. leaflet and advice, joint protection, hand exercises, joint protection and hand exercises) and the reduced statistical power of this model noted. This model will also be used as a secondary analysis to compare the effectiveness of the individual treatments to the leaflet and advice arm.

All analysis models will be adjusted for the baseline value of the outcome of interest (with the exception of the OARSI/OMERACT responder criteria which is not computable at baseline) and also for age, gender, social class, length of time with a hand condition and general practice (covariates defined a priori as those that may influence treatment outcome). Missing data will be imputed using the multiple imputation routines in STATA version 11.0 [57].

A sensitivity analysis will be completed to examine the effectiveness of joint protection and hand exercises for those participants attending all four treatment sessions. This analysis will only be completed if there are sufficient participants attending all four treatment sessions. Treatment concordance will also be evaluated descriptively by (self-reported) frequency and duration of hand exercise completion at 3-, 6- and 12-month follow-up.

Generalisability of the trial findings and the success of the randomisation procedure will be explored descriptively by comparing key characteristics of participants at recruitment and each follow-up stage and for each randomised treatment arm. No interim analyses will be planned during the trial follow-up period.

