#### Randomisation sequence generation, allocation concealment, implementation

Randomisation will be completed at the Arthritis Research UK Primary Care Centre by administrative staff with no clinical involvement in the trial. Details of participants eligible for randomisation will be passed to Centre administrative staff by the research nurse after each research clinic. Administrative staff will enter details of those eligible for randomisation into a Microsoft ACCESS database (housed in a separate geographical location to where the clinical assessments will be conducted). Randomisation will be implemented using random permuted blocks of size 4. The blocks will be selected at random using a random number generator within the ACCESS database and will be selected separately for each GP practice. The randomised treatment of the next patient in the trial will be concealed to both administrative and OT staff until the point of randomisation. Randomisation will be completed using an allocation ratio of 1:1:1:1.

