##### OT Interventions

Participants randomised to any one of the OT interventions will receive in addition to the above, four group sessions held once a week with 4-6 participants. A pool of 12 OTs will be trained to deliver the interventions. In order to develop rapport between participants and therapist it is planned that the same OT will conduct all four sessions. Non-trial co-interventions e.g. splinting, will be avoided during the first six months of the study and recorded if given. To reduce any potential bias, each OT will rotate throughout the interventions every three months. Rotation will be determined by the availability of the OTs to deliver the specific intervention, that is, the single component interventions, or the combined programme.

All three OT interventions will include a general introduction, education on hand OA and its management, and management of pain during everyday activities. The OT interventions will be supported by leader and participant manuals which will be used to promote treatment adherence and to standardise delivery of the OT interventions. Flipcharts will be used as teaching aids, which will identify key points to be addressed within each session, and copies of the pre-written charts will be included in the leader manuals.

Participants will be encouraged to practice techniques taught in the sessions and illustrated in the participant manual, by setting weekly action plans, homework programmes and weekly review of progress. Participants will be encouraged to continue with their own self-management approaches, which they will be asked to record in their participant manual.

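### Class-based delivery in three of the four arms is ignored in the sample size and in the analysis models, so standard errors are too small if outcomes within a class are positively correlated

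*Protocol article*

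**What the plan says.** **Delivery.** Under OT Interventions, the joint protection, hand exercise and combined arms each receive "four group sessions held once a week with 4-6 participants", and "it is planned that the same OT will conduct all four sessions". Twelve therapists are to be trained, and they rotate between the interventions every three months as availability allows. The leaflet arm has no classes. Under Attendance protocol, someone who misses the first session is offered it in a later round, and in some circumstances the same holds for the fourth.

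**Sample size.** Under Target sample size: "This gives a combined improvement of 35% in participants not receiving hand exercises", against 55% with hand exercises, and "with 80% power and alpha of 5%, a total of 212 participants with data at baseline and at 6 months are required". The only further allowance is for attrition: "To allow for a 15% drop-out over the 6 months post randomisation period, 252 participants will be randomized, i.e. 63 per treatment arm". No ICC or design effect appears.

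**Analysis.** Under Statistical methods: "Outcome measures that are continuous will be analysed using analysis of covariance (ANCOVA); for binary outcomes, logistic regression will be used". All models adjust for the baseline value (where it can be computed), age, sex, social class, symptom duration and general practice. No class or therapist effect, mixed model or cluster-robust standard error is named.

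**The concern.** People in the same class share sessions, timing and, as planned, one therapist. Their outcomes may therefore be more alike than those of people in different classes. The design is partially nested: 3 x 63 = 189 participants in roughly 189/6 to 189/4, or 32 to 47, classes, against 63 leaflet participants who are not grouped at all.

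Adjusting for general practice does not deal with this. Practice is the stratum within which randomisation blocks were drawn; it identifies neither the class nor the therapist.

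A model that assumes independence then understates the variance of both factorial contrasts. The error runs one way, towards declaring an effect too readily. It applies to the primary outcome and to every secondary outcome at 3, 6 and 12 months. The protocol fixes the model family, the covariates and a complete sample-size calculation, so this is a stated choice and not a detail deferred to an analysis plan.

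**Working it through.** **Step 1: reproduce the plan's figure.** Inputs from Target sample size: 35% v 55%, 80% power, alpha 5% (taken as two-sided). Allocation is equal ("Randomisation will be completed using an allocation ratio of 1:1:1:1"), so each factorial margin is 1:1.

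n per side = [1.96 x sqrt(2 x 0.45 x 0.55) + 0.8416 x sqrt(0.35 x 0.65 + 0.55 x 0.45)]^2 / 0.20^2 = 95.9, so 96. With the continuity correction it is 105.7, so 106 per side and **212 in total**, an exact match. Then 212/0.85 = 249.4; rounding up to a multiple of four gives 252. The stated figure leaves no room for a design effect.

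**Step 2: variance with clustering.** Evaluable per arm: 212/4 = 53. Responder rates are 25% (leaflet) and 45% (joint protection), as stated; 45% (hand exercise), because the two treatments are assumed equally effective; and 65% (combined), so that the hand-exercise margin averages 55%. The values of p(1-p) are 0.1875, 0.2475, 0.2475 and 0.2275, which sum to 0.91.

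Design effect in the three class arms: DE = 1 + (m-1) x ICC. In the leaflet arm it is 1.

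Variance of the hand-exercise contrast: V = (0.1875 + 0.7225 x DE) / (4 x 53). Unclustered: 0.91/212 = 0.004292, SE 0.0655.

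Variance inflation: VIF = (0.1875 + 0.7225 x DE) / 0.91. Type I error of the unadjusted model: 2 x [1 - Phi(1.96/sqrt(VIF))].

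Power of a correctly clustered test: Phi(d/sqrt(V) - 1.96), where d = 0.20 without the continuity correction and 0.20 - 1/106 with it. By symmetry the joint protection contrast is the same.

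The ICC is an assumption, shown over 0.02 to 0.10. Class size m is 5 (the middle of 4-6) or 5 x 0.85 = 4.25 once 15% attrition is applied.

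| ICC | m | DE | VIF | Type I error | Power, with correction | Power, without |
|---|---|---|---|---|---|---|
| 0 | - | 1 | 1 | 5.0% | 83% | 86% |
| 0.02 | 4.25 | 1.065 | 1.05 | 5.6% | 81% | 85% |
| 0.02 | 5 | 1.08 | 1.06 | 5.7% | 81% | 84% |
| 0.05 | 4.25 | 1.163 | 1.13 | 6.5% | 78% | 82% |
| 0.05 | 5 | 1.20 | 1.16 | 6.9% | 77% | 81% |
| 0.10 | 4.25 | 1.325 | 1.26 | 8.1% | 74% | 78% |
| 0.10 | 5 | 1.40 | 1.32 | 8.8% | 72% | 76% |

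**Step 3: where power reaches 80%.** Without the correction, SE must be 0.20/2.80 = 0.0714. Then V x 212 = 1.080 and DE = (1.080 - 0.1875)/0.7225 = 1.236, so the ICC is 0.236/4 = 0.06 (m = 5) or 0.236/3.25 = 0.07 (m = 4.25). With the correction, the same steps give DE = 1.098 and an ICC of about 0.025 to 0.03.

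**Step 4: sensitivity to the variance basis.** The plan pools each margin and so ignores the other factor. On that basis, with the correction, power starts at 80.1% and at m = 5 falls to 77.5%, 73.7% and 67.7%. The cell-wise figures in the table fit better, because the planned model contains both factors.

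**The case against.** The case for leaving the plan alone has force on size. The ICC is unknown. Manuals, flipcharts and audits standardise delivery, and the primary outcome is self-reported at six months after only four weekly sessions, so a small ICC is plausible. At 0.02 the effect on type I error is under one percentage point. The sample size also carries a continuity correction that the planned logistic regression does not use, which leaves slack. All of this stands. It limits the size of the problem but does not justify a model that assumes the ICC is zero.

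Three stronger readings are tempting, and the document does not support them.

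- *The stated 80% power is not delivered.* This depends on an ICC that the protocol does not give. Without the continuity correction, power stays at or above 80% up to an ICC of about 0.06.
- *Therapist clustering is the larger problem.* Putting about 159/12 = 13 evaluable participants per therapist all in one arm gives VIF of about 1.49 and type I error near 10.8% at ICC 0.05. But therapists rotate between the interventions. If they were fully crossed with the three OT arms, a therapist effect would enter the hand-exercise contrast at half weight. Taking 0.91/4 + 0.015 = 0.2425 as a typical variance in those arms, V is about (0.1875 + 0.95 x 0.7225)/212 + 0.05 x 0.2425/(4 x 12) = 0.0044, so VIF is about 1.02 and type I error about 5.2%. Rotation depends on availability, so the truth lies between these figures, but 10.8% does not describe the planned design.
- *Comparisons of an OT arm with leaflet suffer most.* For class-level clustering the reverse holds, because only one of the two arms is clustered. Joint protection v leaflet at ICC 0.05 and m = 5 has VIF (0.1875 + 1.20 x 0.2475)/0.435 = 1.11 and type I error 6.3%, against 1.16 and 6.9% for the factorial contrast.

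The mechanism should not be overdrawn either. Paired kitchen work is described only for joint protection classes, and one therapist throughout is planned, not guaranteed.

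**Conclusion.** The point holds in a limited form. Three arms are treated in classes, and neither the sample size nor the stated models allow for it. For any positive ICC at class level the planned standard errors are too small.

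The effect on type I error is slight at ICC 0.02 (5.6-5.7%), noticeable at 0.05 (6.5-6.9%) and material at 0.10 (8.1-8.8%). The power claim is at risk only at moderate ICCs: above about 0.025-0.03 with the continuity correction, or 0.06-0.07 without it.

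These figures rest on an assumed ICC range, 53 evaluable per arm, the planned responder rates and 4.25 to 5 evaluable participants per class. The power figures describe a test that allows for clustering. The unadjusted model would appear to lose less power, but only because its type I error is inflated.

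This should be fixed. It is not a reason to enlarge or redesign the trial.

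**What to change.** 1. **Models.** In Statistical methods, allow for class in every primary and secondary model. Either add a random class intercept that applies only in the three OT arms (a partially nested mixed model), or keep the planned ANCOVA and logistic models with standard errors clustered by class and each leaflet participant as a singleton. The second option keeps the planned odds ratio. A mixed logistic model gives an odds ratio conditional on class, which sits awkwardly beside leaflet participants who have no class effect.
2. **Class membership.** Define class as the first round to which the participant was allocated, because sessions can be made up in a later round.
3. **Therapist.** Examine therapist-level clustering as a sensitivity analysis only. With 12 therapists, cluster-robust errors at that level are unreliable.
4. **Data.** Make sure class round and therapist are recorded for each participant. The proforma as described does not list them, though the form itself is not shown.
5. **Power.** State power at 252 randomised (212 evaluable) over an assumed ICC range such as 0.02 to 0.10, and say whether a continuity correction is used.

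**Cost.** Analysis wording and, at most, two fields on an existing form; no extra participants. The price is slightly wider intervals, a less favourable stated power, and a class variance that is estimated imprecisely from about four evaluable people per class.

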#### Health economics

The purpose of economic evaluation is to inform decision makers about competing claims for health care resources. Uncontaminated estimates of costs and effects of alternative treatments are the key parameters for the provision of cost effectiveness evidence and, accordingly, the clinical analytic framework for factorial design randomised controlled trials is not suitable because of the combination of treatment regimens.

The estimation of cost-effectiveness within this 4-arm study will focus on the principles of dominance and extended dominance. Dominance is a straightforward concept; if an intervention is less effective and more costly than at least one of its comparators, it is not for further consideration with regard to the estimation of cost-effectiveness. Extended dominance is applied in incremental cost-effectiveness analysis when an intervention is less effective and more costly than a linear combination of two other strategies; the purpose is to remove from consideration those strategies whose costs and benefits are improved by a mixed strategy of two other alternatives [58]. The practical application of cost-effectiveness analysis is to compare an intervention with the next most effective strategy; failure to remove all dominated or extendedly dominated strategies may lead to comparisons that are not with the next best alternative but with irrelevant alternatives.

In the base case analysis, the estimation of costs relating to the UK National Health Service (NHS) will be based on responses to health care resource use questions within the 6-month and 12-month postal questionnaires; responses will be aggregated to generate a 12-month cost estimate for each responder. The resource use questions will capture details covering a broad range of health care resources, including prescribed medications, primary care and secondary care (inpatient and outpatient) attendances, treatments and investigations. The primary unit of benefit is the quality-adjusted life year (QALY), calculated by applying area-under-the-curve techniques to EuroQol EQ-5D index scores at baseline, 3 months, 6 months and 12 months [59]. The EQ-5D is a generic health status measure that provides utility values for all possible responses to the 5-dimension questionnaire based on health state valuations elicited from a large representative sample of the UK population [60]. The values range from 1.00 (no problems on all dimensions) to -0.59 (severe or extreme impairment on each dimension). Accordingly, the maximum number of QALYs per patient is equal to 1 (equivalent to 12 months spent in full health), with QALYs less than 1 reflecting less than perfect health. Following the identification of appropriate pair-wise comparisons through extended dominance principles, differences in costs and QALYs will be expressed using the incremental cost-per-QALY ratio. This ratio measure provides an estimate of the additional cost necessary to generate one additional QALY. Multiple imputation techniques will be used to deal with missing EQ-5D scores and resource use data, ensuring that all eligible trial participants are included in the base case economic evaluation [61,62].

Probabilistic sensitivity analysis will address uncertainty around the incremental ratio through the application of bootstrap techniques to generate cost-effectiveness planes and acceptability curves [63,64]. Further sensitivity analysis will explore the robustness of the results to variation in key parameters and methodological techniques; namely, the adoption of alternative costing methodologies (e.g. 'generic' verses 'hand OA-specific' health care resource use), a broader analytic perspective that incorporates costs beyond those attributable to the UK NHS, a complete-case analysis to consider the implications of missing data, and the impact of using different generic health status measures to provide utility values.

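### Acceptability curves limited to arms that survive the dominance step would overstate certainty about which of the four options is most cost-effective

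*Protocol article*

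**What the plan says.** The third main research question (Trial Objectives) asks which of the four management approaches is the most cost-effective use of health care resources. For this the Health economics section sets aside the factorial framework and treats the trial as four separate arms.

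The section then gives a sequence:

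- An arm that is less effective and more costly than a comparator is not considered further. Arms beaten by a mixture of two others are also to be removed, and the text warns against failing to remove all of them.
- Next: "Following the identification of appropriate pair-wise comparisons through extended dominance principles, differences in costs and QALYs will be expressed using the incremental cost-per-QALY ratio".
- Last: "Probabilistic sensitivity analysis will address uncertainty around the incremental ratio through the application of bootstrap techniques". This step produces the cost-effectiveness planes and acceptability curves.

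Four further sensitivity analyses are listed: costing method, broader perspective, complete cases, and other utility measures. None revisits the removal step.

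QALYs are "calculated by applying area-under-the-curve techniques to EuroQol EQ-5D index scores at baseline, 3 months, 6 months and 12 months". How QALYs are compared between arms, including any covariates, is not stated.

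On numbers, Target sample size says: "To allow for a 15% drop-out over the 6 months post randomisation period, 252 participants will be randomized, i.e. 63 per treatment arm".

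**The concern.** Dominance is a relation between true mean costs and true mean QALYs. Here it would be judged on estimates from 63 people per arm. If an arm is removed on those estimates and the bootstrap then covers only the ratio between the remaining arms, the acceptability curve gives a removed arm probability zero of being the best choice. The data do not support zero. The probability that belongs to the removed arms is passed to the survivors, and the leading arm looks more secure than it is.

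At stake is the reading of one of the three main questions. The clinical primary analysis is not affected.

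A smaller, related point is precision. Baseline EQ-5D enters the area under the curve and would be expected to correlate with later scores. A chance imbalance at baseline therefore carries into an unadjusted QALY difference.

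**Working it through.** **1. The plan's own figure.** Inputs from Target sample size: 35% against 55%, 80% power, alpha 5% (taken as two-sided), 15% drop-out.

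- Without continuity correction, n per margin = [1.96·√(2·0.45·0.55) + 0.842·√(0.35·0.65 + 0.55·0.45)]² / 0.20² = 95.9, so 96 (total 192).
- With continuity correction, 95.9/4 · [1 + √(1 + 4/(95.9·0.20))]² = 105.7, so 106 (total 212, as stated).
- 212/0.85 = 249.4, so 250. The next multiple of 4 is 252, which is 63 per arm.

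The stated size reproduces. The economic analysis has no sample size of its own and uses these 63 per arm.

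**2. Precision of QALYs at 63 per arm.** Trapezoid weights for 0, 3, 6 and 12 months are 0.125, 0.25, 0.375 and 0.25. The squared weights sum to 0.28125. Assumed, because the article gives no economic SDs: EQ-5D SD 0.25, and correlation 0.7 between any two visits.

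- SD of QALY = 0.25·√(0.28125 + 0.7·0.71875) = 0.221.
- SE of a two-arm difference, unadjusted = 0.221·√(2/63) = 0.039.
- Slope of QALY on baseline = 0.125 + 0.7·0.875 = 0.7375.
- SE of a two-arm baseline difference = 0.25·√(2/63) = 0.0445. A one-SE imbalance moves the QALY difference by 0.7375·0.0445 = 0.033.
- Residual SD after adjustment = √(0.221² − 0.7375²·0.25²) = 0.123. Adjusted SE = 0.123·√(2/63) = 0.022.

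Over SD 0.20 to 0.30 and correlation 0.5 to 0.7, the unadjusted SE is 0.029 to 0.047 and the one-SE shift is 0.020 to 0.039.

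**3. Effect on the acceptability curve.** Simulation with four arms of 63. Assumed: extra mean costs of £0, £60, £60 and £90, cost SD £300, costs independent of QALYs, £20,000 per QALY. Dominance and extended dominance are applied to the sample means. Each bootstrap is approximated by 1,000 normal draws around those means, using unadjusted QALYs, with 3,000 trials per row. On average about 1.7 to 2.1 of the four arms are removed.

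EQ-5D SD 0.25, correlation 0.7:

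| True QALY gain per component | Leading arm, all four arms | Leading arm, survivors only | Probability held by removed arms |
|---|---|---|---|
| 0 | 0.58 | 0.79 | 0.26 |
| 0.02 | 0.61 | 0.79 | 0.23 |
| 0.04 | 0.69 | 0.84 | 0.18 |

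The same simulation over SD 0.20 to 0.25 and correlation 0.5 to 0.7 gives 0.58 to 0.78 with four arms and 0.78 to 0.88 with survivors only. The gap runs from about 0.20 (no QALY effect) down to about 0.11 (SD 0.20, correlation 0.5, gain 0.04).

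**4. What the removal step does not do.** If arm i has lower QALYs and higher costs than arm j, then λQᵢ − Cᵢ < λQⱼ − Cⱼ for every threshold λ ≥ 0. If arm i is beaten by a mixture of j and k, its net benefit is below a weighted average of theirs, and so below the larger of the two. An arm removed on sample means therefore never had the highest sample net benefit. The simulations found no exception.

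**The case against.** The strongest defence has three parts.

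First, removing dominated options before forming incremental ratios is necessary, because ratios against a dominated comparator are meaningless, and the section gives that reason. This stands. The dominance table is right for the point-estimate ratios. It does not follow that removed arms should leave the uncertainty analysis.

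Second, the article does not say in so many words that removal rests on point estimates, that it happens once before any resampling, or that the curves show only survivors. This also stands, and it makes the point one about the natural reading. That reading is still strong: an arm out of consideration has no incremental ratio to bootstrap, and no listed sensitivity analysis brings it back.

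Third, a reader might infer more than the article supports, in two ways.

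- That chance decides which arms are compared, shown by how often the truly best arm falls off the sample frontier (44% of simulated trials with SD 0.25, correlation 0.7 and 0.02 QALY per component). This is not harm done by the dominance step. By step 4 of the working, ranking on net benefit would not have chosen that arm either. It is ordinary sampling error at 63 per arm.
- That QALYs will be compared without adjustment for baseline EQ-5D. No sentence says so. The baseline-adjustment rule under Statistical methods is written for primary and secondary outcomes, and Table 5 lists EQ-5D as tertiary, so that rule does not settle the matter. Silence in a condensed article does not show that adjustment is absent.

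**Conclusion.** The concern holds for the uncertainty analysis. Followed in the order written, the plan leaves removed arms out of the acceptability curves and overstates certainty about the third research question. Under the assumed inputs the leading arm's mean probability of being cost-effective rises from about 0.6–0.7 to about 0.8–0.84. With less variable EQ-5D scores and larger effects both figures are higher and the gap narrows to about 0.11.

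The size rests on assumed SDs, correlations, costs and threshold, and on the survivors-only reading. If the full plan already resamples all four arms, only the wording needs to change.

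Baseline EQ-5D is a request for a statement and not an error found. Its value is precision: in the worked case the SE of a QALY difference falls from 0.039 to 0.022.

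**What to change.** In the paragraph on probabilistic sensitivity analysis, state that all four arms are resampled in every bootstrap replicate, that net monetary benefit is computed for each arm over a range of thresholds, and that one four-option acceptability curve and frontier are presented. Keep the dominance and extended-dominance table to organise the point-estimate ratios, and label it descriptive.

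In the paragraph on QALYs, state that QALY differences are estimated by regression on arm with baseline EQ-5D as a covariate, fitted within the imputation and the bootstrap.

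The cost is a few sentences and slightly more computing. The baseline, 3-, 6- and 12-month EQ-5D scores and the resource-use data are already to be collected, and the cost-per-QALY ratios can still be reported as planned.
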